## 10.6 Lifestyle Considerations

General skin care measures standard for participants with plaque PsO (within the restrictions for topical treatments) are recommended. Participants should avoid excessive sun exposure and avoid risks that are known to provoke flare of PsO.

For the 48 hours prior to scheduled study visits, participants are to refrain from using a sauna, applying emollients to PsO plaques, or drinking alcohol excessively.

## **10.7 Blinding and Randomization of Study Treatment(s)**

### **10.7.1 Part A**

Randomization will take place on Day 1/Week 0 after confirmation that the participant continues to meet the inclusion/exclusion criteria. Participants will be randomized 1:1:1:1:1 to one of 5 treatment arms, stratified by sex and exposure to biologic agents prior to the Screening Visit ([Figure 1](#) and [Table 2](#)).

The IRT will be responsible for the allocation of unique identification numbers to individual participants. Before the study is initiated, the log-in information and instructions for the IRT (including the process for emergency unblinding) will be provided to each site, plus a backup telephone number and call-in directions.

The blind will be maintained by the use of sonelokimab and matched placebo. The prefilled syringes used for all sonelokimab and placebo doses will be identical in appearance. The adalimumab injector will be different in appearance from syringes used for sonelokimab and placebo. However, the study will be blinded at the carton level. The outer packaging will be labeled in a blinded manner with no indication of the syringe contents (sonelokimab, placebo, or adalimumab). Participants will be asked to wear an eye mask for all injections.

### **10.7.2 Part B**

At the beginning of Part B (Week 12) TJC68 and SJC66 response will be assessed in all participants. A responder is defined as a participant who achieves at least a 20% reduction in each of the TJC68 and SJC66 assessments at Week 12 compared with baseline. A non-responder is defined as a participant who does not achieve at least a 20% reduction in each of the TJC68 and SJC66 assessments at Week 12 compared with baseline.

In Part B participants will be allocated to treatment based upon response at Week 12 via the IRT. Treatment assignments in Part A and the allocation for Part B by responders and non-responders at Week 12 are described in [Figure 1](#) and [Table 3](#).

In Part B, the participants and investigators will remain double-blinded to participant treatment. Blinding of participants and investigators will be maintained in the same manner as in Part A.

### **10.7.3 Maintenance of Blinding**

The primary analysis of 12-week data will occur at the completion of Part A, while the study is still ongoing. All sponsor personnel will remain blinded until Week 12. No unblinded participant-level data will be supplied to the study sites until the final database lock after the conclusion of the study.

Laboratory personnel performing the bioanalytical PK sample analysis may receive an open randomization list to enable analysis of relevant samples. In addition, a PK analyst and modeling/simulation scientist may receive an open randomization list to enable preparation of modeling/simulation activities. These individuals will not interact with site or contract research organization personnel.

#### **10.8 Procedure for Breaking the Randomization Code**

Emergency treatment code breaks are to be undertaken only when it is essential to treat the participant safely and efficaciously. Most often, study treatment discontinuation and knowledge of the possible treatment assignments are sufficient to treat a study participant who presents with an emergency condition. The investigator is encouraged to contact the medical monitor prior to code break. Emergency code breaks are performed using the IRT. When the investigator contacts the system to break a treatment code for a participant, they must provide the requested participant identifying information and confirm the necessity to break the treatment code for the participant. The investigator will then receive details of the study treatment for the specified participant and a fax or email confirming this information. [REDACTED]

[REDACTED]

[REDACTED]

It is the investigator's responsibility to ensure that there is a procedure in place to allow access to the IRT in case of emergency. The investigator will inform the participant how to contact their backup in cases of emergency when they are unavailable.

## **11 STUDY ASSESSMENTS AND PROCEDURES**

### **11.1 Screening Assessments**

#### **11.1.1 Psoriatic Arthritis Medical History and Prior Medications**

Relevant PsA medical history is to be collected at the Screening Visit, including time since PsA diagnosis, [REDACTED], and other relevant medical history. [REDACTED]  
[REDACTED]  
[REDACTED]  
[REDACTED]

#### **11.1.2 Medical History and Prior Medications**

Relevant medical history is to be collected at Screening Visit, including history of SARS-CoV-2 vaccinations, drug and alcohol history, smoking history, and other relevant medical history.

#### **11.1.3 Demographics**

Demographic and disease characteristics will be collected including, but not limited to:

- Sex;
- Race;
- Ethnicity;
- Year of birth.

#### **11.1.4 QuantiFERON TB Gold Testing**

QuantiFERON TB Gold testing (or IGRA equivalent) will be conducted at screening to evaluate the participants' eligibility for the study. This blood-based assay is specific for *Mycobacterium tuberculosis* and is not influenced by previous BCG vaccination or by exposure to other mycobacterial species. The assay measures the production of interferon-gamma and presents it relative to a negative and a positive control sample. Details on the collection, shipment of samples and reporting of results by the central laboratory are provided to investigators in the study Laboratory Manual.

Participants with evidence of TB infection as defined by a positive QuantiFERON TB-Gold test (or IGRA equivalent) at screening are excluded unless the following criteria apply:

- A full TB work-up (according to local practice/guidelines) completed within 12 weeks prior to randomization establishes conclusively that the participant has no evidence of active or latent TB. Participants with evidence for active TB are excluded;
- Participants positive for latent TB per work-up must have completed sufficient treatment according to local routine clinical practice at least 4 weeks before randomization.

If a QuantiFERON TB Gold test (or IGRA equivalent) at screening is indeterminate, it can be repeated once. The results of the second test are to be used. If the second QuantiFERON TB Gold test is also indeterminate, the participant should be managed as for participants with positive QuantiFERON TB Gold test (or IGRA equivalent).

If there is reasonable medical doubt about a potentially false-positive QuantiFERON TB-Gold test (or IGRA equivalent) result, the test can be repeated once after obtaining Medical Monitor approval, and the results of the second test will prevail.

### 11.1.5 Hepatitis B and Hepatitis C Testing

Participants with known hepatitis B virus (HBV) or hepatitis C virus (HCV) infections will be excluded.

At screening, all participants will be tested for hepatitis B and C antibodies. Participants who are HCV core antibody positive (Ab+) must undergo further testing for HCV RNA by the central laboratory. HCV RNA must be negative per the central laboratory to allow further participation into the study.

Hepatitis B screening will follow the testing strategy illustrated in [Figure 2](#).

**Figure 2 Interpretation and Management of HBV Serologic Test Results**

[figure not shown]

Abbreviations: HBc Ab = hepatitis B core antibody; HBs Ag = hepatitis B surface antigen; HBV = hepatitis B virus; PCR = polymerase chain reaction

- a A positive test result for HBs Ab is expected for participants who have had a HBV vaccination. For participants without a history of HBV vaccination (and where mandated by local requirements), a positive result for HBs Ab requires HBV DNA PCR testing.

#### **11.1.6 Human Immunodeficiency Virus Testing**

Participants with known HIV infections at screening will be excluded. All participants will be tested at screening for HIV. Participants testing positive for HIV will be excluded from study participation. Samples for testing will be analyzed by the central laboratory. Details for the collection and handling of samples for HIV testing are in the Laboratory Manual.

#### **11.1.7 SARS-CoV-2 Testing**

At screening, all participants will be tested for SARS-CoV-2 (nasopharyngeal PCR test). The screening test will be performed by the central laboratory. If sample collection for the central laboratory is not possible at sites due to local procedures, a test may be obtained at a suitable laboratory as long as evidence is provided and retained as source data. The local test must be collected between 2 days prior and 3 days post-screening visit.

If a participant tests positive for SARS-CoV 2 infection at screening, another PCR or antigen test may be performed within the screening window. If the repeat test is negative and the participant is asymptomatic, they may enter the study.

#### **11.1.8 Height and Weight**

Height will be measured at screening. Weight will be measured at screening and at other study visits according to the SOA in Section 3, Table 1.

### **11.2 Efficacy Assessments**

Efficacy assessments will be conducted according to the SOA in in Section 3, Table 1. For assessor-rated scales, the site will make every effort for each participant to be rated by the same site personnel at each time point.

#### **11.2.1 Composite Disease Assessments**

Composite disease assessments, such as ACR20/50/70, [REDACTED] minimal disease activity [REDACTED] used in this study are automatically calculated using results from assessment scales completed by participants or investigators (or qualified designees), and are not to be calculated manually by the investigator or study personnel.

##### **11.2.1.1 American College of Rheumatology 20/50/70**

The ACR response criteria [Felson D.T. et al., 1995] is a composite measure in which the improvement is observed in the number of swollen joints, number of tender joints, and the following 5 criteria: patient global assessment, physician's global assessment, functional ability measure (i.e., HAQ), visual analog pain scale, and hs-CRP.

ACR20 response is:

- At least a 20% improvement in TJC68;
- At least a 20% improvement in SJC66;

- At least a 20% improvement in at least 3 of the following 5 variables:
  - PtAAP;
  - PtGADA;
  - PhGADA;
  - HAQ-DI;
  - hs-CRP.

ACR50 response is:

- At least a 50% improvement in TJC68;
- At least a 50% improvement in SJC66;
- At least a 50% improvement in at least 3 of the following 5 variables:
  - PtAAP;
  - PtGADA;
  - PhGADA;
  - HAQ-DI;
  - hs-CRP.

ACR70 response is:

- At least a 70% improvement in TJC68;
- At least a 70% improvement in SJC66;
- At least a 70% improvement in at least 3 of the following 5 variables:
  - PtAAP;
  - PtGADA;
  - PhGADA;
  - HAQ-DI;
  - hs-CRP.

[figure not shown]

### 11.2.1.3 Minimal Disease Activity

Criteria for assessing minimal disease activity, listed below, covering all of the domains of the disease have been developed to determine whether the participant has reached minimal disease activity based on key outcome measures in PsA. Minimal disease activity is defined as meeting 5 of the 7 following criteria:

1. TJC68  $\leq 1$ ;
  2. SJC66  $\leq 1$ ;
  3. PASI  $\leq 1$ , or PsO affecting  $\leq 1\%$  of BSA;
  4. PtAAP  $\leq 15$  on a 0 to 100 VAS;
  5. PtGADA  $\leq 20$  on a 0 to 100 VAS;
  6. HAQ-DI  $\leq 0.5$ ;
  7. LEI  $\leq 1$ .
- [figure not shown]

### 11.2.2 Patient Reported Outcomes

[figure not shown]

#### **11.2.2.2 Patient's Global Assessment of Disease Activity**

The PtGADA will be self-administered by the participant at visits indicated in the SOA in Section 3, Table 1.

The PtGADA will be performed using a horizontal 100 mm VAS, ranging from 0 (very well) to 100 (very poor) after the question: "Considering all the ways PsA affects you, please indicate with a vertical mark ( | ) through the horizontal line how well you are doing today."

#### **11.2.2.3 Patient's Assessment of Arthritis Pain**

The pain-VAS will be self-administered by the participant at visits as indicated in the SOA in Section 3, Table 1.

The PtAAP will be performed using a horizontal 100 mm VAS, ranging from 0 (no pain) to 100 (severe pain) after the question: "Please indicate with a vertical mark ( | ) through the horizontal line the most pain you had from your psoriatic arthritis today."

#### **11.2.2.4 Health Assessment Questionnaire Disability Index**

The HAQ-DI [Bruce B. et al., 2003] will be self-administered by the participant at visits as indicated in the SOA in Section 3, Table 1.

The HAQ-DI is a twenty-item PRO instrument that assesses current physical function/disability. The HAQ-DI covers 8 categories (dressing and grooming, hygiene, arising, reach, eating, grip, walking, and common daily activities). There are 4 response options, ranging from 0 (no difficulty) to 3 (unable to do). HAQ-DI score is reported as a mean score between 0 and 3 by dividing the total score by the number of items answered. The HAQ-DI has been the most-widely used instrument to assess physical function in clinical studies of treatments for rheumatoid and PsA and has extensive evidence of its validity and other psychometric properties in this context.

#### **11.2.2.5 Short-Form-36 Health Survey-Version 2**

The SF-36v2 [Ware J. et al., 1993] will be self-administered by the participant at visits as indicated in the SOA in Section 3, Table 1.

The SF-36v2 is a 36 item generic HRQoL instrument that uses a recall period of 4 weeks. Items are grouped into 8 domains as follows:

1. Limitations in physical activities because of health problems;
2. Limitations in social activities because of physical or emotional problems;
3. Limitations in usual role activities because of physical health problems;
4. Bodily pain;
5. General mental health (psychological distress and well-being);
6. Limitations in usual role activities because of emotional problems;
7. Vitality (energy and fatigue);
8. General health perceptions.

Each question has 5 answers scored 1 (unable to) to 5 (no difficulty). The scale score of each domain is calculated based on the summed score across items included in the domain and is rescaled to 0 to 100. Version 2 of the SF-36 questionnaire will be used in the study.

In addition to domain scores, the PCS and MCS scores are calculated from the 8 domains. Component scores appreciate the impact of each domain on physical and mental health status [Maruish M.E., 2011]. Each of the 8 domain scores and the component summary scores range from 0 to 100, with a higher score indicating a better health status. The 2 component summary scores are standardized with a mean of 50 and standard deviation (SD) of 10 in the general US population. Component summary scores for a study timepoint are to be calculated from the domains completed at that same timepoint.

The SF-36v2 PCS combines 4 scales: limitations on physical activities because of health problems, limitations in usual role activities because of physical health problems, bodily pain, and general health perceptions.

The SF-36v2 MCS combines the remaining 4 scales: limitations in social activities because of physical or emotional problems, general mental health (psychological distress and well-being), limitations in usual role activities because of emotional problems, and vitality (energy and fatigue).

#### **11.2.2.6 Functional Assessment of Chronic Illness Therapy-Fatigue**

The FACIT-Fatigue [Webster K. et al., 2003; Yellen S.B. et al., 1997] will be self-administered by the participant at visits as indicated in the SOA in Section 3, Table 1.

FACIT-Fatigue is a 13-item self-assessment of fatigue and the effect on daily activities and function over the previous 7 days. The 13 items use a 5-point Likert-type scale as follows:

- 0 = “Not at all;”
- 1 = “A little;”
- 2 = “Somewhat;”
- 3 = “Quite a bit;”
- 4 = “Very much.”

The 13 scores are summed to create a single fatigue score.

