## Scoring Derivations

Several instruments will be used in this study to measure some underlying construct. As such, missing data in this type of instruments can occur on the item scores. Missing data will be handled as described by the author of each instrument and detailed in the relevant endpoint section, or, if no information is stated by the author, no imputation will be done and such scores (and any resultant domain/total score) will remain missing.

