#### **8.6.4.12 Functional Assessment of Chronic Illness Therapy-Fatigue (FACIT-Fatigue)**

Other secondary endpoints include:

- Change from baseline in Functional Assessment of Chronic Illness Therapy-Fatigue (FACIT-F) score

FACIT-Fatigue is a 13-item self-assessment of fatigue and the effect on daily activities and function over the previous 7 days (See [Appendix H](#)). The 13 items use a 5-point Likert-type scale (0 = “Not at all”, 1 = “A little”, 2 = “Somewhat”, 3 = “Quite a bit”, 4 = “Very much”). The FACIT-Fatigue assessment score range between 0-52 with 0 corresponding to the highest level of fatigue and 52 corresponding to the lowest level of fatigue. The scores for the 11 items where a higher score indicates more fatigue are reversed (4-score) before being summed together with the other 2 items to give the total. If any items are missed, then the total score is adjusted by multiplying by 13 and dividing by the number of items answered.

The FACIT-Fatigue will be self-administered by the participant at Baseline, Week 4, Week 12, Week 16 and Week 20.

The exploratory null hypotheses to be tested are that the mean change from baseline over time are not different for the comparisons of interest. To test these hypotheses, a MMRM will be used including the Part A visits as detailed in section 8.6.1.2

Descriptive summaries by treatment group and visit will also be displayed for Part A and Part B.

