## **9 CHANGES TO PLANNED ANALYSIS FROM STUDY PROTOCOL**

An additional sensitivity analysis targeting treatment policy where response is analyzed regardless of intercurrent events will also be performed on the primary endpoint.

The sensitivity estimand will also include subjects who discontinued due to adverse events.

Logistic regression estimator approach for population-level difference of proportions will be used instead of logistic regression with multiple covariates.

Composite endpoints for ACR+PASI are added.

LOCF/NRI analysis is added for responder parameters and LOCF for continuous.

BASDAI derivation is re-calculated according to SAP.

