Appendix H: FACIT-Fatigue Scale

Below is a list of statements that other people with your illness have said are important. Please select one number per line to indicate your response as it applies to the past 7 days.

|                                                                          | Not
at all | A little
bit | Some-
what | Quite
a bit | Very
much |
|--------------------------------------------------------------------------|---------------|-----------------|---------------|----------------|--------------|
| HI7
I feel fatigued
.....                                          | 0             | 1               | 2             | 3              | 4            |
| HI12
I feel weak all over
.....                                    | 0             | 1               | 2             | 3              | 4            |
| An1
I feel listless (“washed out”)
.....                           | 0             | 1               | 2             | 3              | 4            |
| An2
I feel tired
.....                                             | 0             | 1               | 2             | 3              | 4            |
| An3
I have trouble starting things because I am tired
..... | 0             | 1               | 2             | 3              | 4            |

[figure not shown]

|      |                                                                              |   |   |   |   |   |
|------|------------------------------------------------------------------------------|---|---|---|---|---|
| An4  | I have trouble finishing things because I am tired
.....           | 0 | 1 | 2 | 3 | 4 |
| An5  | I have energy
.....                                                       | 0 | 1 | 2 | 3 | 4 |
| An7  | I am able to do my usual activities
.....                                 | 0 | 1 | 2 | 3 | 4 |
| An8  | I need to sleep during the day
.....                                      | 0 | 1 | 2 | 3 | 4 |
| An12 | I am too tired to eat
.....                                               | 0 | 1 | 2 | 3 | 4 |
| An14 | I need help doing my usual activities
.....                               | 0 | 1 | 2 | 3 | 4 |
| An15 | I am frustrated by being too tired to do the things I want
to do
..... | 0 | 1 | 2 | 3 | 4 |
| An16 | I have to limit my social activity because I am tired                        | 0 | 1 | 2 | 3 | 4 |

[figure not shown]

[figure not shown]

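### SAP 8.6.4.12 prorates FACIT-Fatigue with no minimum number of answers, so a single answered item yields a full 0–52 score (minor)

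*Combined protocol and SAP*

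**What the plan says.** Protocol 11.2.2.6 describes a 13-item questionnaire with answers from 0 to 4 and says that "The 13 scores are summed to create a single fatigue score". It gives no reversal, range, direction or rule for missed items.

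SAP 8.6.4.12 is specific. "The scores for the 11 items where a higher score indicates more fatigue are reversed (4-score) before being summed" with the other two. The range has "0 corresponding to the highest level of fatigue and 52 corresponding to the lowest level of fatigue". For incomplete forms, "If any items are missed, then the total score is adjusted by multiplying by 13 and dividing by the number of items answered". No minimum number of answers is stated.

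SAP Appendix H reproduces the form. Eleven items are worded like "I feel fatigued", where 4 is worse. Two, one on having energy and one reading "I am able to do my usual activities", are worded so that 4 is better.

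Elsewhere the SAP does set floors. HAQ-DI is not calculated unless at least 6 of its 8 categories are answered (8.6.2.4). An SF-36v2 scale is not scored if fewer than 50% of its questions are answered (8.6.4.13).

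The general rule in SAP 7.3.1, under Scoring Derivations, is that "Missing data will be handled as described by the author of each instrument and detailed in the relevant endpoint section". SAP section 9, which lists departures from the protocol, includes "BASDAI derivation is re-calculated according to SAP" but nothing on FACIT-Fatigue.

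**The concern.** Proration assumes that the unanswered items would have averaged the same as the answered ones. That is reasonable when most of the form is complete and weak when almost none of it is. Under the rule as written, a questionnaire with one answer gets a total on the full scale, and the model cannot tell it from a complete one. At baseline the damage spreads, because the baseline score is both subtracted from every later visit and used as a covariate (SAP 8.6.1.2).

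At stake is the quality of one patient-reported secondary endpoint. A smaller, separate matter is that someone scoring from the protocol sentence alone would get a total pointing the wrong way.

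**Working it through.** **Inputs.** Thirteen items scored 0–4; 11 reversed and 2 not (SAP 8.6.4.12, Appendix H); multiplier 13/k for k items answered (SAP 8.6.4.12); about 40 participants per arm (SAP 5.5).

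**1. Reproduce the SAP range.** Let N be the raw sum of the 11 fatigue-worded items (0–44) and P the raw sum of the other two (0–8). SAP total = (44 − N) + P.
- Most fatigue, N = 44 and P = 0: 44 − 44 + 0 = 0.
- Least fatigue, N = 0 and P = 8: 44 − 0 + 8 = 52.

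This agrees with the stated 0–52.

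**2. Score a form with one answer.** Total = 13 × (that item after any reversal), giving 0, 13, 26, 39 or 52. A single fatigue-worded item answered 4 gives (4 − 4) × 13 = 0, the worst possible total. Each point on an item moves the total by 13/k: 13 points for k = 1, 13/7 = 1.86 for k = 7, and 1 for k = 13.

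**3. How noisy is it?** Assume, for illustration, that items have equal SD. If they are independent, the SD of a prorated total relative to a complete form is √(13/k): 3.61 for k = 1 and 1.36 for k = 7. If they are perfectly correlated the ratio is 1. The documents give no inter-item correlation, so the one-item ratio lies somewhere between 1 and 3.61 for non-negatively correlated items.

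**4. Bound on the error.** Proration replaces 13 − k unknown items, each between 0 and 4, so it can miss the complete-form total by at most 4 × (13 − k): 48 points for k = 1 and 24 for k = 7. One such form in an arm of 40 moves that arm's unadjusted mean by at most 48/40 = 1.2 or 24/40 = 0.6 points. These are extremes, not expectations.

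**5. What floor fits the SAP's own practice?** Half of 13 is 6.5, so the smallest count that meets the SF-36v2 standard is 7 (7/13 = 54%; 6/13 = 46%).

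**6. The protocol sentence read literally.** Total = N + P.

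| Record | Literal protocol sum | SAP total |
|---|---|---|
| Most fatigue (N = 44, P = 0) | 44 | 0 |
| Least fatigue (N = 0, P = 8) | 8 | 52 |
| One-point improvement on every item (N falls 11, P rises 2) | −9 | +13 |

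Changing the sign does not convert one into the other, because P enters both with the same sign. A literal sum of 26 means N = 26 − P, so the SAP total is 18 + 2P, anywhere from 18 to 34.

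**The case against.** The strongest reply on the floor is SAP 7.3.1, which ties missing-item handling to the instrument author's method. That method may contain a minimum, and the source papers are not available here to check. But the same sentence says the handling is detailed in the endpoint section, and that section states proration without a limit. A programmer working from 8.6.4.12 would apply none. If the author's rule has a minimum, it needs to be written there.

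A second reply is that nearly empty forms will be rare: questionnaires are completed at site visits (protocol 8.3.2) and some are captured electronically (protocol 15.1). That is plausible and limits the size of the problem. The documents give no rate of partial forms, and state no completeness check for this one.

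On the protocol sentence, a reader might infer that the two documents hold rival scoring rules and that the endpoint could be reported with its sign reversed. The documents do not support that. Protocol 11.2.2.6 omits the reversal; it does not rule it out. Protocol 12.3 leaves technical detail to the SAP, SAP section 1 says the SAP provides the data derivations, and 8.6.4.12 gives a complete rule that fits the form in Appendix H. A reversed result would require someone to disregard the SAP. Nor is the BASDAI entry in section 9 an exact parallel: there the protocol gave a full formula that the SAP replaced, whereas here it gave an incomplete description that the SAP completed.

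**Conclusion.** The missing floor is a real gap in the SAP's own rule, and it is out of step with how the SAP treats HAQ-DI and SF-36v2. The protocol wording is a documentation mismatch only; the SAP rule is correct and should govern.

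Severity is minor. FACIT-Fatigue is an other secondary endpoint with exploratory testing only (SAP 8.6.4 and 8.6.4.12). The primary endpoint, key secondary endpoints, type I error control and sample size do not depend on it. The practical effect is probably small, on the assumption, which the documents neither give nor bound, that very incomplete questionnaires are few. The one-item score follows directly from the rule as written. The noise ratio rests on the equal-SD assumption and a range of correlations, and the shifts in arm mean are worst-case bounds for a single form.

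**What to change.** Add one sentence to SAP 8.6.4.12: *The prorated score is calculated only if at least half of the items (7 of 13) are answered; otherwise it is missing.* The threshold is proposed to match the SAP's 50% standard for SF-36v2 and is not taken from a figure in the documents. If the instrument's published method sets a different minimum, state that one.

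Add one line to SAP section 9, next to the BASDAI entry, noting that 8.6.4.12 completes protocol 11.2.2.6 by reversing 11 items and fixing the 0–52 range and its direction. This does not need a protocol amendment by itself; the protocol sentence can be tidied if the protocol is amended for another reason.

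The cost is two sentences of SAP text. A few very incomplete questionnaires become missing and are handled by the planned model under its missing-at-random assumption (SAP 7.3.1). A participant whose baseline form falls below the floor would have no change score for this endpoint.
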